### **The intervention: 3 consent procedures**

Patients who receive the opt-out plus procedure (the patient is actively informed about the option to opt-out from research with residual tissue) and the informed consent procedure (the patient is asked for broad written consent for research with residual tissue) will receive specific information from their treating physician or a nurse practitioner by using a standardized text and a special information leaflet which is more extensive than the information leaflets currently available in the hospitals. In principle, this information will be given during a planned visit at the clinic. When this is impossible, the intervention might be conducted through telephone.

The consent procedures:

1. Opt-out plus. In this procedure patients will receive verbal and written information, and a specific leaflet (attachment F) on the use of residual tissue in research including an opt-out form. Patients can opt-out by returning this form using a stamped envelope.
2. Informed consent. In this procedure patients will receive verbal and written information and a specific leaflet (attachment G) on the use of residual tissue in research with a consent form to provide explicit written consent. Patients are asked to return the consent form using the

stamped envelope, indicating whether or not they consent to the use of their residual tissue in future research.

3. Opt-out (control). This group of patients will receive usual care. They may read information about the use of residual tissue in research in the (general) information leaflet of the hospital.

Patients in the two intervention arms will be informed by the medical staff using a standardized text (see below), which takes approximately one minute.

### **Standardized texts (see attachments O and P for Dutch versions)**

1. Opt-out plus: “Shortly <<tissue type>> will be removed. This tissue will be examined and stored in case it is necessary for your treatment that it is examined again. This tissue may also be used in scientific research. We want to ask you whether your stored tissue may be used for scientific research. It is important for the hospital that tissue is available for scientific research, because research on new methods of treatment and diagnosis often uses residual tissue. This brochure contains more information about residual tissue. Could you read the brochure? If your residual tissue can be used for scientific research, you do not have to do anything. If you do not want your residual tissue to be used for scientific research, you can fill in the form attached to the brochure and return it to us in the stamped envelope.”

2. Informed consent: “Shortly <<tissue type>> will be removed. This tissue will be examined and stored in case it is necessary for your treatment that it is examined again. This tissue may also be used in scientific research. We want to ask you whether your stored tissue may be used for scientific research. It is important for the hospital that tissue is available for scientific research, because research on new methods of treatment and diagnosis often uses residual tissue. This brochure contains more information about residual tissue. Could you read the brochure, indicate whether or not your residual tissue can be used for scientific research, and return the form to us in the stamped envelope?”

### **Questionnaires and interview**

Data on patient characteristics, medical history and experiences with research and genetic testing will be obtained through a questionnaire, while clinical data, including the diagnosis, will be obtained from the medical records of patients. All recruited patients will be asked to complete a questionnaire (see below) six weeks after the intervention or six weeks after surgery for the control group. The questionnaire will be mailed to their home address, which will be retrieved from the patients’ medical files. For non-respondents a written reminder will be sent after one month and a second reminder will be given by telephone (including a structured non-response item list).

In 25% of the respondents, including all participants who did not consent to research with their residual tissues, a structured telephone interview (see below) will be conducted (provided respondents gave permission to be interviewed) to obtain supplementary, qualitative data about the experience with the consent procedure. These respondents will be equally distributed over hospitals, conditions and intervention arms, besides the respondents who did not consent to research with their tissues. Mixed methods research is especially suited for exploring complex situations and allows for a representation of patient experience and preferences both in quantitative (social facts paradigm) and qualitative (social

construction paradigm) data. The method is used because consent procedures (specifically the difference between opting-out and providing written consent) are complex matters which may be evaluated by patients in a different way according to situation but especially according to the type of research for which consent is solicited (see also preliminary results). Further, all respondents will be sent a second questionnaire (see below) six months after their decision (i.e. consent or not, or opt-out or not) to assess whether they are still satisfied with the decision they made earlier.

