## **Study objectives**

The main part of this study aims to determine patient preferences for and satisfaction with consent procedures regarding the use of residual tissue for research, to provide insight into the type of information patients need to decide on the use of their material in research, and to determine the optimality of the timing and the content of these procedures in clinical practice. We will compare the three consent procedures, opt-out, opt-out plus and informed consent, with respect to the following primary study outcomes:

1. Patients' satisfaction with and preference for a consent procedure
2. Proportion of patients aware of storage of tissue and research use
3. Consent rates
4. Medical staff's satisfaction with and preference for a consent procedure

Additionally, we will obtain information on (1) the proportion of non-consent due to non-response; (2) the characteristics of non-consenters and non-respondents; and (3) the reasons for providing or withholding consent or (non-)response. We will investigate how patients perceived the information they received about residual tissue use and their knowledge about this topic. Patients' preferences to provide or withhold consent for specific types of research (e.g. genetic, commercial) and feedback regarding unanticipated findings will be investigated as well. Further, we will examine whether consent rates, satisfaction with or preference for a consent procedure differ according to severity of disease, type of clinical procedure (e.g., biopsies or surgical removal of tissue), diagnosis, type of hospital (academic or community) or demographics. Six months after the first questionnaire, we will examine whether patients are still aware of the decision they made and whether they are still satisfied with their choice to provide or withhold consent.

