### **Study design including study arms**

In this multicentre randomized controlled trial, 1800 patients will be recruited from academic and community hospitals during an 18 month period (Figure 2). The consent procedures will be offered a short time before or after the tissue or blood is removed, dependent on what is the best timing according to the clinician or nurse practitioner. Patients to be included are

distributed over four hospitals: two academic hospitals and two regional hospitals: the NKI-AVL, the Vrije Universiteit Medical Center (VUmc), the Spaarne hospital in Hoofddorp and the Kennemer hospital in Haarlem. Inclusion of academic and community hospitals will increase the external validity (i.e. generalizability) of the study results.

Patients will be randomized, stratified by hospital and diagnosis, to opt-out plus, informed consent or opt-out (control group) in collaboration with [name] (statistician NKI-AVL). Clinicians and nurse practitioners who will carry out the intervention will receive envelopes that each contain the paperwork (checklist, brochure in opt-out plus and informed consent arms and return envelopes) for one patient. The envelopes will be put in order of the randomization. Clinicians and nurse practitioners will write down his or her name, the patient's name, patient number, diagnosis, date and method of tissue removal on the checklist. A random selection of diagnoses on the checklists will be compared with the diagnoses in the medical files to check their validity. If the validity is found to be poor, all diagnoses will be checked.

In our previous intervention study (see preliminary results) we asked patients informed consent before the start of the intervention. However, patients felt that it was confusing to be asked informed consent for a study in which they were asked to provide informed consent. To prevent this kind of confusion in the current study, we will not ask consent for the randomization and the intervention. We believe that not asking consent for the randomization is suitable to our study because the informed consent procedure bears no potential harm to the participants, the intervention is of importance for future clinical research, the intervention includes no invasive procedure for the participants, and at least the standard care is offered to participants in the control group.

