### **Data collection: first questionnaire (see attachment B)**

The first questionnaire consists of several parts. All questions have been developed for this study, based on the questionnaire of our previous intervention study, unless otherwise indicated.

- Questions to measure patients' knowledge about residual tissue use. These questions have been developed for this study.
- Questions about how patients perceived the information about residual tissue use (both brochures and verbal information) they received, and how they would have liked to be informed.
- Questions to assess whether patients were aware of the fact that they could have had an influence on residual tissue use and if so, which decision they made.
- Questions to assess patients' satisfaction with the consent procedure and their preferences for a consent procedure.
- Questions about what types of research patients want to give consent for (commercial research, different types of diseases, research in other hospitals), and how often they want to give consent (once or for each new protocol).
- Questions to assess feelings of ownership of the tissue, trust in research or the hospital, and how important they feel scientific research is. Some of these questions were developed by the Rathenau Institute.
- Questions to assess whether patients want feedback on unexpected findings in their residual tissue and whether not receiving feedback would influence their decision about residual tissue use.
- Questions about previous experiences with scientific research and tissue removal. Some of these questions were developed by the Rathenau Institute.
- Questions about demographics.
- Two subscales of the SF-12 to assess physical functioning and mental health.
- The PSQ-18, or Patient Satisfaction Questionnaire 18 will be used to assess patient satisfaction with medical care. The questionnaire has been developed based on a larger questionnaire, the PSQ-III. The original, English version of the PSQ-18 has been validated and demonstrated to be reliable (<http://www.rand.org/content/dam/rand/pubs/papers/2006/P7865.pdf>). Further, the Dutch version of the PSQ-III (Patienten Tevredenheidsvragenlijst) has been validated and demonstrated to be reliable. In this study, we will use three subscales of this scale, namely general satisfaction, interpersonal manner, and communication. Each subscale consists of two items.

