## ***Basic plan of analysis***

Analysis will first be performed to evaluate the comparability of the intervention groups and the control group at study entry in terms of sociodemographic and clinical characteristics. Student's t-test or appropriate non-parametric statistics will be used, depending on the level of measurement. If the groups are found not to be comparable on one or more background variables, those variables will be employed routinely as covariates in subsequent analyses using multivariate models, such as logistic regression.

The proportion of the outcomes in each intervention arm, i.e. consent rates and patients' satisfaction with and preference for a consent procedure, the proportion of patients aware of storage of tissue and research use, and the satisfaction with and preference for a consent procedure of the medical staff, will be evaluated by comparison of the informed consent

versus the opt-out plus group, and the opt-out plus versus the opt-out group by non-parametric or parametric tests as appropriate. Patient characteristics, satisfaction with and preferences for the information and consent procedures will be evaluated according to patient characteristics such as age, educational level, sex, hospital type, type of clinical procedure, and disease type. All analyses will be performed using SPSS.

A qualitative analysis of the information needs and appreciation of the patients for the consent procedures will be evaluated through questions in the questionnaire and telephone interviews with a representative group of patients who completed the questionnaire.

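### Adjusting or stratifying consent rates on variables known only for questionnaire respondents may understate non-consent in the informed consent arm

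*Protocol*

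**What the plan says.** **Source of the variables.** Under Questionnaires and interview: "Data on patient characteristics, medical history and experiences with research and genetic testing will be obtained through a questionnaire". The same sentence goes on: "while clinical data, including the diagnosis, will be obtained from the medical records of patients". The list of items in the first questionnaire includes "Questions about demographics". It is mailed six weeks after the intervention (after surgery for controls), and Study sample expects 75% to respond.

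**Known for everyone.** Randomisation is "stratified by hospital and diagnosis", and staff write down, for each patient, "patient number, diagnosis, date and method of tissue removal on the checklist" (both in Study design including study arms).

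**Use in the analysis.** Basic plan of analysis compares the arms "at study entry in terms of sociodemographic and clinical characteristics". If they differ on a background variable, "those variables will be employed routinely as covariates in subsequent analyses using multivariate models", with logistic regression as the example. The next paragraph names consent rates among the outcomes and makes no exception for them.

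**Denominator.** Sample size, statistical power justifies up to 600 per arm by subgroup analysis and adjustment. It then applies the 75% response and counts on 450 per group, stratified by 3 to 4 factors into subgroups of 90 to 150. That sentence calls the contrast one of response rate, but its figures, 0.1% versus 10%, are those used for non-consent just before.

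**Outcome.** Consent or opt-out is given on a form separate from the questionnaire (The intervention: 3 consent procedures). Study objectives also asks for "the proportion of non-consent due to non-response".

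**The concern.** As far as the protocol states, sociodemographic variables such as education exist only for patients who return a questionnaire after the intervention. Two things follow.

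First, such variables cannot show comparability at entry of all patients randomised. A difference between arms among respondents may reflect unequal response by arm rather than the allocation.

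Second, a consent-rate model that contains such a variable has no covariate value for non-respondents. If they are left out, the analysis keeps only people who mail paperwork back, and willingness to do so is part of what separates the arms. In the informed consent arm a patient must return a form to give consent. In the two opt-out arms, doing nothing leaves the tissue available. Selecting on questionnaire return can therefore remove non-consenters from essentially one arm. The consent contrast also feeds the rule under Outcomes for choosing the procedure that serves research best, so its estimate matters as well as its significance.

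**Working it through.** **Inputs from the protocol.** 600 per arm; 75% questionnaire response; non-consent 10% (informed consent) versus 0.1% (opt-out or opt-out plus).

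**1. The protocol's own denominator.** 600 × 0.75 = 450 per arm, and 1800 × 0.75 = 1350 in all. This reproduces. It leaves 150 per arm (450 of 1800) without questionnaire variables.

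(The 121 per group given for this contrast does not follow from its stated inputs, which give 95 with continuity correction. That is a separate matter, errs on the safe side, and has no bearing here.)

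**2. Which arm can lose non-consenters.** Informed consent: 0.10 × 600 = 60. Each opt-out arm: 0.001 × 600 = 0.6. Selection can lower the rate by at most 0.1 percentage point in an opt-out arm, but by up to 10 points in the informed consent arm.

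**3. Rate seen among respondents.** Let p be non-consent in respondents and RR the ratio of non-consent in non-respondents to that in respondents. RR is an assumption; no figure in the protocol informs it. Then

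0.75p + 0.25 × RR × p = 0.10, so p = 0.10 / (0.75 + 0.25 × RR).

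| RR | Respondents (450) | Non-respondents (150) | Understatement, points |
|---|---|---|---|
| 1 | 10.0% | 10.0% | 0 |
| 2 | 8.0% | 16.0% | 2.0 |
| 3 | 6.7% | 20.0% | 3.3 |
| 4 | 5.7% | 22.9% | 4.3 |

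Check for RR = 3: 30/450 = 6.7% and 30/150 = 20%; 30 + 30 = 60.

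Against the planned contrast of 10 − 0.1 = 9.9 points, the shortfall is 0 at RR 1, 2.0/9.9 = 20% at RR 2 and 4.3/9.9 = 43% at RR 4.

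**4. Power** against 0.1% (two-sided 0.05, without continuity correction).

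| Respondent rate | 450 per arm | 150 per arm | 90 per arm |
|---|---|---|---|
| 10% | above 99.9% | 98% | 86% |
| 6.7% | above 99.9% | 89% | 69% |
| 5% | 99.7% | 77% | 55% |

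The main comparison keeps its power. The harm there is a biased estimate. Power suffers only in the small subgroups.

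**The case against.** A reader might infer that all covariates come from the questionnaire. They do not: clinical data come from the records, hospital and diagnosis are stratification factors, and method of tissue removal is on the checklist.

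A reader might also infer that the main consent-rate contrast is biased toward zero. The protocol does not support that. It compares proportions between arms with ordinary tests, and that comparison need lose nobody. Covariates enter only on observed imbalance, which may never arise or may concern only record variables; the protocol itself expects education and sex to be balanced. Loss of patients also presumes complete-case handling, and a method for missing covariates may well stand in a statistical analysis plan not shown here.

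Nor do the documents support a very large bias. Nothing in them links an unreturned consent form to an unreturned questionnaire. If only 10% of the 60 non-consenters returned a questionnaire, the respondent rate would be 6/450 = 1.3%. But that needs 54/150 = 36% non-consent in non-respondents, about 27 times as much. Some non-consenters will have mailed back a refusal, so they do return paperwork.

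Finally, the protocol plans to describe non-respondents and has a telephone non-response item list, whose content is not shown. It also calls 75% a conservative figure.

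All of this stands and limits the point. It does not remove two stated choices: questionnaire variables as evidence of comparability at entry, and 450 respondents as the base for stratified consent-rate work. The second does not depend on the imbalance condition. Imputing covariates would repair neither.

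**Conclusion.** The point holds in conditional form. If a sociodemographic variable triggers adjustment and patients without a questionnaire are excluded, or if the 450 is used as denominator, the adjusted or stratified estimate may understate non-consent, mainly in the informed consent arm. With 10% true non-consent and 75% response, the understatement is nil if consent and questionnaire return are unrelated, and 2.0 to 4.3 points if non-consent is two to four times as frequent in non-respondents. That ratio is illustrative.

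Two further assumptions are inferred rather than stated: that consent status can be established for every randomised patient from the separate form, and that an unreturned form in the informed consent arm counts as non-consent. The objective on non-consent due to non-response supports the second reading. This is worth correcting, but it does not threaten the main test.

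**What to change.** In Basic plan of analysis, and for the 450 denominator in Sample size, statistical power:

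- Analyse consent rates in all randomised patients. Count an unreturned form in the informed consent arm as non-consent, and report that component separately.
- Adjust for hospital and diagnosis and, if wanted, for procedure type, age and sex taken from checklist or record.
- Show comparability of the arms on these variables for all randomised patients.
- Use questionnaire variables only in models for questionnaire outcomes, and label them characteristics of respondents.

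The cost is wording, plus taking age and sex from the record if they are used. The consent-rate model would not adjust for education, which is a minor loss in a randomised trial. In return the consent-rate analysis keeps 600 rather than 450 per arm.

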### **Methods**

In this multicentre, randomized controlled trial, 1800 patients will be recruited from four hospitals in the Netherlands (expected response rate 75%). Patients will be randomized to three study arms. In the ‘informed consent’ and ‘opt-out plus’ arms, patients are informed about residual tissue use both verbally and through a specific leaflet. These leaflets contain a consent form and an opt-out form respectively. In the third arm, the control group, no (extra) information about residual tissue use is offered, and patients may opt-out of the use of their residual tissue verbally or written. Patients to be included will be stratified by hospital and condition. Two academic and two regional hospitals will be included. Inclusion of both categories of hospitals and of patients with malignant and non-malignant diseases will increase the generalizability of the study results.

Six weeks after the intervention, patients will receive a questionnaire addressing satisfaction with and preference for the consent procedures. One quarter of the respondents will be interviewed about these topics through a semi-structured telephone interview. Six months after the intervention, respondents will receive a second questionnaire to examine whether those who made a decision about the use of their residual tissue are still aware of that decision and, if they are, whether they are still satisfied with it.

Clinicians and nurses who will carry out the interventions will receive a pre- and post-experimental questionnaire to examine their opinions about and experiences with the consent procedures.

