## ***Burden for the patients / respondents***

Usual care is offered to patients in the control group. In both intervention groups patients receive brief verbal information and a leaflet, after which they are either asked to sign a consent form or to sign an opt-out form if the patients wants to opt-out. The procedures in the two intervention arms bear no harm to patients. Six weeks after the intervention, patients are asked to fill in a questionnaire. This will take about 45 minutes. 25% of the respondents will be interviewed by telephone, which will take about 20 minutes. Respondents will be sent a second questionnaire, which will take about 10 minutes to fill in. Based on our previous experiences, it is unlikely that the intervention procedures, filling in the questionnaires, or participating in the interview will cause any distress for respondents.

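### The first questionnaire is timed from a different event in the control arm than in the two active arms, and the second questionnaire has three conflicting dates

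*Protocol*

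**What the plan says.** **First questionnaire.** Protocol, *Questionnaires and interview*, sends it "six weeks after the intervention or six weeks after surgery for the control group". Two other places give one clock for patients in general. The Summary, under *Methods*, has "Six weeks after the intervention, patients will receive a questionnaire addressing satisfaction with and preference for the consent procedures", and *Burden for the patients / respondents* has "Six weeks after the intervention, patients are asked to fill in a questionnaire". Control patients receive usual care and so have no intervention to count from.

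**When the intervention happens.** *Study design including study arms* states: "The consent procedures will be offered a short time before or after the tissue or blood is removed". The clinician or nurse practitioner chooses, and no limit in days is set. The scripts for both active arms open with "Shortly <<tissue type>> will be removed", which implies that information comes first.

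**Second questionnaire.** Three start points are given:
- Summary, *Methods*: "Six months after the intervention, respondents will receive a second questionnaire".
- *Study objectives* in the main text: "Six months after the first questionnaire, we will examine whether patients are still aware of the decision they made".
- *Questionnaires and interview*: "six months after their decision (i.e. consent or not, or opt-out or not".

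**Who is included.** *Study sample* lists 1600 patients with surgery or biopsy and 200 with blood drawing. Staff note the date and method of tissue removal on a checklist, and the list of attachments includes a checklist for the opt-out arm.

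**The concern.** In a randomised comparison, outcomes should be measured at the same point in every arm. Here the mailing rule itself sets a different start event for controls, and randomisation does not undo that. Satisfaction, awareness, stated preference and willingness to respond may all move with recovery and recall. A difference in elapsed time between control and active arms could then be read as an effect of the consent procedure.

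The exposed contrasts matter to the trial. Two hypotheses compare both active arms with opt-out on satisfaction and on awareness. *Basic plan of analysis* includes opt-out plus versus opt-out. The patient criteria in *Outcomes* use satisfaction and awareness to choose the best procedure.

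There is also a practical fault. From the text as written, staff cannot derive a first mailing date for a control patient who had no surgery, or a single second mailing date for anyone.

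**Working it through.** The plan states no figure for this point, so there is none to reproduce. The check is a comparison of the timing statements plus date arithmetic.

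**1. First questionnaire, days since removal**

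Inputs: six weeks = 42 days (protocol). *L* = days by which the intervention precedes removal, negative if it follows. The protocol gives no value for *L*, so the values below are assumed.

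- Control, where surgery is the removal: 42
- Active arms: 42 − *L*
- Difference, active minus control: −*L*

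| Assumed *L* (days) | Active arms | Control | Difference |
|---|---|---|---|
| −14 | 56 | 42 | +14 |
| −7 | 49 | 42 | +7 |
| 0 | 42 | 42 | 0 |
| 7 | 35 | 42 | −7 |
| 14 | 28 | 42 | −14 |

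A lead of 28 days would give 42 − 28 = 14 days, but four weeks is hard to square with a short interval. The shift in an arm's mean is minus the mean of *L*, so a mixture of before and after partly cancels. The scripts point to positive *L*, which means active patients would answer sooner after removal than controls.

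**2. Which comparisons are exposed**

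- Informed consent versus opt-out plus: same clock, so the rule creates no difference.
- Either active arm versus control, on questionnaire outcomes: exposed.
- Consent by returned form in the active arms, and staff outcomes: not dependent on this mailing.

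**3. Controls without surgery**

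The 200 blood-draw patients and an unstated number of biopsy patients are not described by the word surgery. If the 200 split evenly over three arms, about 200 / 3 ≈ 67 are controls, plus the biopsy controls.

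**4. Second questionnaire, days after the intervention**

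Inputs: six months ≈ 182.6 days. *d* = days from intervention to decision, not stated, assumed 0 to 42.

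- Counted from the intervention: 182.6 days (182.6 / 7 ≈ 26 weeks)
- Counted from the first questionnaire: 42 + 182.6 = 224.6 days (224.6 / 7 ≈ 32 weeks)
- Counted from the decision: 182.6 + *d*, i.e. 182.6 to 224.6 days

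The first two differ by 42 days. The third may coincide with the first. It has no date when *d* does not exist: agreeing patients under opt-out plus need do nothing, most controls need do nothing, and some informed consent patients may not return the form. Controls also have no intervention date. No section reconciles the three.

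**5. With removal as the common anchor**

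Days since removal at the first questionnaire are 42 in every arm, a difference of 0. Days since information in the active arms become 42 + *L*, for example 56 for *L* = 14 and 28 for *L* = −14.

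**The case against.** The strongest reply is that controls have no intervention, so some substitute date is unavoidable, and that time since being informed is a sensible clock for recall of that information and satisfaction with it. Anchoring on removal moves the same gap elsewhere: if it is two weeks, active patients answer about eight weeks after being informed instead of six. The remedy therefore cannot call the gap large as a fault and small as a cost.

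This is fair, and it bears on which anchor to choose. It does not justify different anchors by arm. Time since information has no counterpart in the control arm and cannot be equalised there, whereas time since removal can. The variation that remains falls within the active arms and should be similar in both.

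It is also fair that the gap is unstated, described only as short, and possibly zero or reversed, and that no bias in any outcome has been estimated. The missing surgery date is partly loose wording, since the checklist captures a tissue removal date. However, the protocol does not say that a date is recorded for blood draws.

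A reader might infer that arm and measurement time are confounded for all primary patient outcomes and cannot be disentangled. The documents do not support that. The two active arms share a clock, and recorded dates would allow some adjustment. Nor do the three second-questionnaire dates confound arm with time: none is assigned by arm, and that questionnaire serves additional aims outside the four listed primary outcomes.

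**Conclusion.** The point holds in a limited form. Following the text builds an arm-dependent interval into contrasts with control on questionnaire outcomes: satisfaction, awareness, preference and response. Its size equals the gap between intervention and removal. It is zero for same-day information and one to two weeks in either direction if the short interval means that, which is an assumption. The scripts suggest that active patients would answer earlier after removal. The effect on the outcomes themselves cannot be quantified from the protocol.

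The second-questionnaire problem is a separate contradiction. Two of its start points are about six weeks apart, and the third is undefined for patients who return no form. It would be wrong to say that all three definitions differ by at least six weeks, because the decision date may lie anywhere from zero days after the intervention.

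Both faults should be corrected, since mailing dates are trial conduct. Later analysis could at best adjust for unequal timing.

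**What to change.** Define one index date in the same way for all three arms and count both mailings from it. An example is the date of tissue or blood removal taken from the checklist. Confirm that the checklist also records this date for blood draws, and replace the word surgery so that biopsy and blood drawing are covered. Then make the Summary *Methods*, the main-text *Study objectives*, *Questionnaires and interview* and *Burden for the patients / respondents* agree.

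The cost is protocol wording and a mailing rule. The downside is that time since being informed will vary within the active arms by the gap between intervention and removal, similarly in both. Record the intervention date for each active-arm patient so that this can be examined. If the investigators prefer another common anchor, it should be one that exists for every patient, including controls and those who return no form.
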